## Abstract

**Background:**

Emerging evidence suggests that children become fatter and less fit over the summer holidays but get leaner and fitter during the in-school period. This could be due to differences in diet and time use between these distinct periods. Few studies have tracked diet and time use across the summer holidays. This study will measure rates of change in fatness and fitness of children, initially in Grade 4 (age 9 years) across three successive years and relate these changes to changes in diet and time use between in-school and summer holiday periods.

**Methods:**

Grade 4 Children attending Australian Government, Catholic and Independent schools in the Adelaide metropolitan area will be invited to participate, with the aim of recruiting 300 students in total. Diet will be reported by parents using the Automated Self-Administered 24-h Dietary Assessment Tool. Time use will be measured using 24-h wrist-worn accelerometry (GENEActiv) and self-reported by children using the Multimedia Activity Recall for Children and Adults (e.g. chores, reading, sport). Measurement of diet and time use will occur at the beginning (Term 1) and end (Term 4) of each school year and during the summer holiday period. Fitness (20-m shuttle run and standing broad jump) and fatness (body mass index *z*-score, waist circumference, %body fat) will be measured at the beginning and end of each school year. Differences in rates of change in fitness and fatness during in-school and summer holiday periods will be calculated using model parameter estimate contrasts from linear mixed effects model. Model parameter estimate contrasts will be used to calculate differences in rates of change in outcomes by socioeconomic position (SEP), sex and weight status. Differences in rates of change of outcomes will be regressed against differences between in-school and summer holiday period diet and time use, using compositional data analysis. Analyses will adjust for age, sex, SEP, parenting style, weight status, and pubertal status, where appropriate.

**Discussion:**

Findings from this project may inform new, potent avenues for intervention efforts aimed at addressing childhood fitness and fatness. Interventions focused on the home environment, or alternatively extension of the school environment may be warranted.

**Trial registration:**

Australia New Zealand Clinical Trials Registry, identifier ACTRN12618002008202. Retrospectively registered on 14 December 2018.

## Background

One in six children in OECD countries is classified as overweight or obese [1]. Overweight or obese children are at increased risk of developing non-communicable diseases [2], thereby establishing childhood overweight and obesity as a serious public health concern. There is also evidence showing that children’s aerobic fitness is worse today than several decades ago [3]. Childhood fatness as well as lower muscular and aerobic fitness track moderately well into adulthood, being associated with poorer adult health and higher mortality [4, 5]. Thus, strategies to address overweight and obesity and increase aerobic and muscular fitness levels during childhood are warranted.

Emerging research, predominantly conducted in North America, shows that increases in fatness and declines in aerobic fitness occur at a much greater rate during the school summer holiday period, compared with the school year [6–10]. These negative health outcomes are more pronounced among children who are already overweight or obese or from low socio-economic backgrounds [6]. Thus, the school summer holiday period is identified as a high-risk period for unfavourable changes in body composition, and declines in aerobic fitness, and may be an overlooked critical window for intervention.

Obesogenic behaviours, particularly children’s dietary intake (i.e. energy and nutrient intake, dietary pattern/quality [11]) and daily time use (i.e. time spent in physical activity, sedentary behaviour/screen time, sleep), as well as their environments (e.g. school and home), all play a role in facilitating or limiting increases in fatness or declines in fitness. Previous obesity interventions have predominantly been delivered in schools, and have had limited success [12]. The “Structured Days Hypothesis” provides a possible explanation for this, suggesting that obesity interventions may have more success if they target unstructured days (that is, days with few scheduled activities, such as school summer holidays), rather than the structured days (e.g. in-school period) [13]. The school day provides children with consistent structure, routine, and adult supervision, and provides all children with opportunities for favourable obesogenic behaviours. These include scheduled physical activity opportunities (e.g. physical education, recess and lunch), regulated caloric intake (e.g. school food and beverage availability, guidelines and/or legislation) and set meal/snack times, potentially limiting opportunities for unhealthy weight gain and declines in fitness [13]. In contrast, children may engage in more unfavourable obesogenic behaviours (e.g. poorer diet, more sedentary time and less physical activity) on less structured days (e.g. when at home during the school summer holidays). This could explain why children return to school fatter and less fit after the summer holidays [13].

There are few studies comparing children’s diet and time use during the school and summer holiday periods, and findings are mixed [14–18]. Some studies reported children had less favourable or similar diets during the school holidays, compared with the school year [14, 15], and engaged in more screen time during the school holidays (3.6 ± 1.5 h/day), compared with during the school term (3.1 ± 1.6 h/day) [15]. One study found that total daily energy expenditure (TDEE) during holidays (adjusted TDEE = 2450 ± 270 kcal/day) was not significantly different from TDEE during school term (adjusted TDEE = 2510 ± 350 kcal/day) among 6–13 year-olds at risk of overweight/obesity [16]. In contrast, others reported physical activity was higher during the school holidays, compared with school term [14, 15]. These studies are limited by the use of independent samples for school and holiday periods, and/or not specifically measuring the holiday period (i.e. weekend days were used as a proxy for school holidays), and by the omission of sleep duration [14–16]. In addition, they considered children’s activities such as screen time and physical activity as independent variables rather than as co-dependent parts of a 24-h day. If the time spent in some activities changes when children go on summer holidays, then the time spent in other activities must also change to compensate because there are only 24 h in a day. For a comprehensive exploration of changes in time-use behaviours, 24-h data are needed, and analytical methods appropriate for co-dependent variables should be used [19, 20].

One study of 366 Australian children compared 24-h time use on school days and holidays in the same children using analytical methods for co-dependent variables (compositional data analysis) [21]. During holidays, children slept an extra 40 min, accumulated 58 min more screen time and spent 10 min less in vigorous-intensity physical activity. Estimated TDEE was 5% lower. Further research is warranted to explore whether unfavourable changes in diet and time use occur over the summer holiday period.

### Aims and hypotheses

The focus of this research is to determine rates of change in fitness and fatness during in-school and summer holidays across successive school years, and to relate rates of change in these outcomes to changes in diet and time use. Specific hypotheses are:
Rates of change in fitness and fatness will differ between in-school and summer holiday periods.The difference between in-school and summer holiday rates of change in fitness and fatness will differ according to the child’s socio-economic position (SEP), sex and weight status.Differences in rates of change in fitness and fatness between in-school and summer holiday periods will be associated with differences in diet and time use between in-school and holiday periods.

## Methods/design

### Study design

A 3-year longitudinal study with rolling recruitment occurring over two years; participants will be followed for three successive years. Ethical approval has been obtained from University of South Australia Human Research Ethics Committee, Adelaide, Australia (200980), the South Australian Department of Education and Child Development (2008–0055) and the Adelaide Catholic Education Centre (201820).

### Participants and recruitment

Participants will be children, in Grade 4 (age approx. 9 years) at the time of enrolment, who attend a Government, Catholic or Independent primary school in the Adelaide metropolitan area. All Government, Catholic and Independent primary schools in the Adelaide metropolitan area (*n* = 334) will be manually categorised into tertiles according to their Index of Community Socio-Educational Advantage (ICSEA) score. The ICSEA provides an indication of socio-educational backgrounds of students and is based on parents’ occupation, parents’ education, geographical location and the proportion of indigenous students [22]. Schools will be randomly selected from tertiles with a probability proportional to the number of children enrolled. Selection of schools will continue progressively until at least 100 students in schools from each of low, middle and high tertiles have been recruited.

Principals from eligible schools will be invited to participate initially via email, and then be contacted via telephone one week later. A researcher will meet with all interested principals or their delegates to explain the requirements of study participation. Participating principals will be provided with a plain language statement and consent form to be signed and returned prior to commencement. All children in Grade 4 from each school will be invited to participate. Once consent is obtained from school principals, children in Grade 4 will be provided with an information pack containing an information sheet and consent form to take home to their parents/guardians. Written consent from parents prior to study participation, and verbal assent from children at each measurement occasion will be required. Assuming 24 students per class [23], 42 Grade 4 students per school [24] and a 50% response rate, approximately 14 schools will need to be recruited. As compensation for their time and commitment to the research project, at the end of each study year schools will receive $500 and the parents of each participating child will receive a $50 voucher. Each participating child will receive an age-appropriate gift at the conclusion of the study, as well as a small gift after each accelerometer administration to encourage return of the equipment.

### Measures

The schedule of assessments across the study period is shown in Fig. 1. Diet and time use (accelerometry and 24-h recall) assessments will be conducted at the beginning (Term 1) and end (Term 4) of each school year and during each summer holiday period (December/January) for study years 1 and 2. Anthropometric and fitness measures will be taken at the beginning and end of each school year. Trained research personnel will administer fitness and fatness assessments in school, during usual school hours.

**Fig. 1 Fig1:**
[figure not shown]
Schedule of assessments across the study period. The blue shaded areas indicate the holiday periods

### Time use

Wrist-worn GENEActiv accelerometers will be used to provide a measure of children’s time spent sleeping, sitting and in light-, moderate- and vigorous- intensity physical activity. Accelerometers will be worn 24 h/day for 7 consecutive days. The GENEActiv has excellent convergent validity (r = 0.98) when compared to other accelerometers [25]. Intra-instrument and inter-instrument reliabilities are also strong (CV_intra_ = 1.4% and CV_inter_ = 2.1%), and it shows very good test-retest reliability (ICC = 0.67–0.87) [26]. The accelerometers will be distributed and collected from the children’s school at the beginning and end of each 7-day wear period and mailed to participants during school holiday periods with reply paid envelopes. A researcher will instruct children about accelerometer wear and care and provide children with an information leaflet to take home to their parents, following standardised protocols. Participants will also be provided with a paper self-report form where they will record their sleep and wake times, periods of device removal, along with the reason for removal. Data will be collected at 50 Hz and collapsed into 60-s epochs. The cut-points identified by Phillips et al. [27] will be used to identify durations of sedentary time, light- and moderate-vigorous physical activity. The algorithm proposed by van Hees et al. [28] will be used to derive sleep characteristics. Participants’ accelerometry data will be included in analyses if they wear the accelerometer for at least 10 waking hours, on at least three weekdays and one weekend day.

Specific types of activity will be captured using the Multimedia Activity Recall for Children and Adults (MARCA), a computerised 24-h recall [29]. Participating children will recall every activity (e.g. sports, reading, household chores) they did over a 2-day period during 30-min face-to-face interviews (terms 1 and 4) and during computer-assisted telephone interview (summer holidays). This will be done using a segmented-day format with a resolution of 5 min or more. Participants will choose from 500 activities, yielding a high-resolution snapshot of how they used their time. The MARCA has evidence of good validity (r = 0.4–0.7) when compared against accelerometry [29], pedometry [30] and doubly-labelled water [31], and excellent test-rest reliability (ICC = 0.88–1.00) [29]. Each activity is linked to a compendium of energy expenditures [32] so that overall and activity-specific energy costs can be estimated. Where possible, the same two days will be recalled at each time-point, including at least one weekday and one weekend day, overlapping where possible with GENEActiv data.

### Diet

Dietary intake will be assessed using the Automated Self-Administered 24 h Dietary Assessment Tool (ASA24), Australian version (2016), developed by the National Cancer Institute, Bethesda, MD, United States [33]. The ASA24 is an online tool for collecting 24-h dietary recall data using the seven-pass method (i.e. meal-based quick list, meal gap review, detail pass, forgotten foods, final review, last chance, usual intake) with digital photographic measures to aid portion size estimation [34, 35]. For children younger than 10 years, parent- or proxy-reported dietary intake is required [36, 37]. The ASA24 will be interviewer administered. Parent/carer proxy recalls will be undertaken via phone with the child present where possible so children can provide information on food and drinks consumed in the absence of the parent/carer. At each study time point, parents/carers will complete the ASA24 on one occasion (~ 30 min/recall), recalling food and drinks consumed over the previous 24-h. At the group level weekday and weekend days will be recalled. A second recall will be collected in a sub-sample of 10% to enable estimate of usual intake. Compared to dietary intake assessed via the plate wastage method, the ASA24 estimates energy intake within 0.52 kcal (95% CI − 236, 237) when self-administered by adults (i.e. parents/carer) [38]. Food group intake, energy and nutrient intake will be estimated using the Australian Food Supplement and Nutrient Database (AUSNUT) 2011–3 [39]. Usual energy and macronutrient intake will be derived using the web-based statistical modelling technique Multiple Source Method [40, 41].

Primary outcomes will be fitness and percentage body fat. Waist circumference and body mass index will be assessed as secondary outcomes.

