**Fig. 2 Fig2:**
[figure not shown]
Mock data for changes in aerobic fitness. The blue shaded areas indicate the holiday periods. The black dots are measured values; the white dots are estimated fitness levels when extrapolated to the start, or back-extrapolated to the end of the holiday periods

Time use will be quantified as 24-h activity compositions [61]. These activity compositions will consist of mutually exclusive and exhaustive parts of the day which together sum up to 24 h. Accelerometry compositions will capture daily times spent in energy expenditure bands (sleep, sitting, light, moderate and vigorous PA), and MARCA compositions will capture times spent in activity “types” (e.g. chores, physical activity, school). The average daily accelerometry and MARCA time-use compositions will be used for analyses. Compositions will be expressed as isometric log ratios [62] to enable their inclusion in the linear mixed effects models. Differences in rates of change in outcome variables (S–H) will be regressed against differences between the in-school composition (C_S_) and the holiday composition (C_H_) (C_S–H_) to test Hypothesis 3 (∆_S–H_ is correlated with C_S–H_). Compositional isotemporal substitution analysis [63] will be used to quantify the change in fitness and fatness when replacing a given quantum of one component of the activity composition (e.g. 30 min of sitting) with the same quantum of another (e.g. 30 min of moderate- to vigorous- intensity physical activity), while holding the remaining components constant. A similar analysis will be performed for diet, with macronutrient mix or food group intake as the composition, and total energy intake as a covariate. Analyses will adjust for age, sex, SEP, parenting style, weight status, and pubertal status, where appropriate.

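### Diet rests on one recall per time point with day type covered only across the group, so a weekday–weekend difference enters many of the within-child diet contrasts used for Hypothesis 3

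*Protocol article*

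**What the plan says.** The Diet section fixes the number of recalls: "At each study time point, parents/carers will complete the ASA24 on one occasion". On day type it says only: "At the group level weekday and weekend days will be recalled". It adds two elements aimed at usual intake: "A second recall will be collected in a sub-sample of 10% to enable estimate of usual intake", and "Usual energy and macronutrient intake will be derived using the web-based statistical modelling technique Multiple Source Method". Food groups are not named in that last sentence, and no day-type term is mentioned.

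The Measures section sets the time points. Diet and time-use "assessments will be conducted at the beginning (Term 1) and end (Term 4) of each school year and during each summer holiday period", with summer holidays covered in study years 1 and 2. A child therefore has two term recalls per school year, one recall per summer holiday, and two holiday periods in all.

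The Analysis section (text after Fig. 2) defines the Hypothesis 3 contrast: "Differences in rates of change in outcome variables (S–H) will be regressed against differences between the in-school composition" and the holiday composition. It extends this to diet: "A similar analysis will be performed for diet, with macronutrient mix or food group intake as the composition". The covariates listed there are demographic, family, weight and pubertal variables; the day of the recall is not one of them.

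For the activity recall (MARCA), the Time use section does state a within-child rule: "Where possible, the same two days will be recalled at each time-point", with both a weekday and a weekend day among them.

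**The concern.** Recalling both day types across the sample serves a population mean. Hypothesis 3 needs something else: the difference within each child between term diet and holiday diet. With a single recall at each point, one child may be recalled on a weekday in term and a weekend day in the holidays, and another the other way round. Each child's difference then contains a weekday–weekend component that has nothing to do with the change from school to holiday.

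If recall day is unrelated to the change in fitness or fatness, this component is noise in the exposure, and it tends to pull the estimated diet associations towards zero. The protocol handles the matter within child for the activity recall, and requires both weekdays and a weekend day for valid accelerometry. Diet rests on the fewest days of the three and has no stated within-child control of day type. At stake is the diet part of Hypothesis 3, not the primary comparison of rates of change.

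**Working it through.** The protocol gives no figure for day-type mismatch, so there is none to reproduce. The check asks how often a child's in-school and holiday values would differ in day type, and how much noise that adds.

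**Inputs from the protocol**
- One recall per time point (Diet).
- Two term time points per year and one holiday time point (Measures).
- A second recall in 10% of children (Diet).

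**Assumptions, not in the protocol**
- Weekend share of recalls, *p*: from 2/7 (proportional to the calendar) to 1/2 (equal split), the same in term and holidays.
- Day types independent across a child's recalls.
- A common weekday–weekend diet gap *D* in term and holidays.

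**Step 1: share of children with mismatched day types.** With *k* term recalls set against one holiday recall, the day-type mix agrees only if all *k* + 1 recalls are of one type:

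P(mismatch) = 1 − [*p*^(k+1) + (1 − *p*)^(k+1)]

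This equals 2*p*(1 − *p*) for *k* = 1 and 3*p*(1 − *p*) for *k* = 2.

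| | *p* = 2/7 | *p* = 1/2 |
|---|---|---|
| *k* = 1 (one term recall) | 20/49 = 40.8% | 50% |
| *k* = 2 (Term 1 and Term 4) | 210/343 = 61.2% | 75% |

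For *k* = 1 and a common *p* the share cannot exceed 50%. For *k* = 2 it passes 50% once 3*p*(1 − *p*) > 0.5, that is, once *p* exceeds 0.21. At *p* = 0.20 the shares are 32% (*k* = 1) and 48% (*k* = 2).

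**Step 2: size of the noise.** The mismatch share is only a count. The day-type part of a child's difference is *D* times the difference in weekend share between term and holiday, so its SD is:

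SD = *D* × √[*p*(1 − *p*)(1 + 1/*k*)]

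| | *p* = 2/7 | *p* = 1/2 |
|---|---|---|
| *k* = 1 | √(0.2041 × 2) = 0.64*D* | √(0.25 × 2) = 0.71*D* |
| *k* = 2 | √(0.2041 × 1.5) = 0.55*D* | √(0.25 × 1.5) = 0.61*D* |

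Averaging two term recalls raises the share of children with some mismatch but lowers the SD. The SD is the figure that bears on attenuation.

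**Step 3: effect of the 10% second recall.** Suppose, generously, that every child in the subsample became fully matched. The shares are multiplied by 0.9:
- *k* = 1: 0.9 × 40.8% = 36.7%, to 0.9 × 50% = 45%.
- *k* = 2: 0.9 × 61.2% = 55.1%, to 0.9 × 75% = 67.5%.

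**Step 4: what cannot be computed.** Attenuation depends on the day-type variance relative to the rest of the variance in the diet difference. The protocol gives neither *D* nor the day-to-day variance of a single recall.

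**The case against.** Several objections have force.

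- **The protocol is silent, not contrary.** With one recall per time point a child cannot cover both day types, so the group-level sentence may simply describe coverage across children. It does not say that a child's day type varies between time points, and an article may leave call scheduling to the full protocol. This stands as a limit: independence is an assumption. But the only rule stated for diet works at group level, while a within-child rule is stated for the activity recall.
- **A reader might infer that most children are mismatched.** That holds only if Term 1 and Term 4 both form the in-school value and *p* exceeds 0.21. The protocol states neither how that value is formed nor the weekend share.
- **A reader might infer that a null diet result would be uninformative.** The protocol does not support this, because without *D* the attenuation cannot be sized.
- **A reader might treat a term recall on a weekend day as a mistake.** The exposure is the in-school period, which includes weekends. A weekend share of 2/7 (29%) represents that period fairly. The trouble is the unmatched difference, not the presence of weekend days.
- **The MARCA rule cannot be carried over.** It needs two days per time point; diet has one. A strict same-type rule that switched type each year would leave half of child-years with no school-day diet, against (2/7)² = 8% with both term recalls on weekends under independence at *p* = 2/7. Any matching rule has to allow for this.
- **Mitigation exists.** The second recall and the Multiple Source Method help in part. The first reaches 10% of children; the second is stated for energy and macronutrients only, although food groups may be the composition.
- **Model terms may sit in an analysis plan that is not shown.** That is possible for the covariate. An analysis plan cannot, however, re-match days once the recalls are collected.

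**Conclusion.** The point holds as a moderate design weakness confined to the diet analysis of Hypothesis 3. Day type is controlled across the group where the analysis needs control within the child, and the listed covariates do not make up for it.

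Under the stated assumptions, roughly 40% to 75% of children would have mismatched day types, depending on how the in-school value is formed, with noise of 0.55*D* to 0.71*D* in the exposure difference. The expected direction is attenuation, provided that recall day is unrelated to outcome change; the amount is unknown. If the weekday–weekend gap is smaller in the holidays than in term, the noise is smaller than these figures. A null diet finding would be harder to interpret, but the documents do not support a stronger statement. The primary outcomes and Hypothesis 1 are not affected.

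**What to change.** **For all recalls, including those already collected**
- Record the day type of each recall.
- Include day type in the usual-intake model, and apply that model to food groups if they are used as a composition.
- Adjust the Hypothesis 3 diet model for each child's in-school minus holiday difference in weekend share. If the day-type gap may differ between term and holidays, enter the two weekend shares separately.
- Add a sensitivity analysis restricted to children whose in-school and holiday recalls are of the same day type.
- State how the in-school diet value is formed from Term 1 and Term 4.

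**For recalls still to be booked**
- Match day type within child between term and holiday where possible, and ensure that each child has at least one matched weekday pair over the two holiday periods.

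**Cost.** No extra recalls are needed. The price is less freedom in booking calls, one or two model degrees of freedom, and a smaller sample in the sensitivity analysis. Child-years matched on weekend days would contain no school-day diet, which is why the weekday pair is required.
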